## **3.0 GENERAL ANALYSIS DEFINITIONS AND CONVENTIONS**

### **3.1 Ancillary Component**

#### **3.1.1 Analysis Populations**

##### **3.1.1.1 Screened Population**

The screened population consists of all participants who provided verbal consent at the initiation of the screening process. Pre-study participants are not included.

##### **3.1.1.2 Primary Ancillary Analysis Population**

The primary ancillary analysis population includes the first 75 planned participants who completed informed consent for the Ancillary component during screening. Pre-study participants are not included.

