#### 12.6.6 Analysis for Ancillary Study

The primary objective of the ancillary study is to determine the proportion of participants with COWS < 8 that:

- a) experience a 5 or greater point increase in COWS score within 4 hours of XR-BUP administration

- b) transition to moderate withdrawal (COWS 13-24) within 4 hours of XR-BUP
- c) meet clinician determined criteria for precipitated withdrawal within 1 hour of XR-BUP administration

Proportions will be estimated along with 95% confidence intervals using the Exact Clopper-Pearson method.

Our *a priori* hypotheses are that:

- a) fewer than 20% of those with a COWS score < 8 experience a 5 or greater point increase in COWS score within 4 hours of XR-BUP administration (i.e., 95% upper confidence limit < 20%)
- b) <10% patients transition to moderate withdrawal (COWS 13-24) within 4 hours of XR-BUP administration (i.e., 95% upper confidence limit < 10%)
- c) <10% patient experience precipitated withdrawal events within 1 hour of XR-BUP administration (i.e., 95% upper confidence limit <10%)

If these hypotheses are confirmed, and with approval of the steering committee and DSMB, we will modify eligibility criteria for the Effectiveness RCT component to allow patients with COWS < 8 to enter the RCT component. If these are not confirmed, the data will be reviewed with the DSMB to get their recommendation as to which patients, if any, with a COWS < 8 should enter the RCT component.

We will also examine the cumulative proportions (assessed at ½ h intervals) of participants that experience these events by timepoint using logistic regression with GEE. Sensitivity analyses may be conducted as well to evaluate the effect of changes in eligibility criteria, such as estimating the above proportions before and after the changes in eligibility criteria.

Secondary outcomes including vital signs (BP, HR, respiratory rate), COWS, OOWS and Adjective scores, pupillary diameter, craving, bad drug effects, pain assessment, local tolerability and post injection medications will be assessed during the 4-h following XR-BUP administration. Changes over time will be evaluated using linear mixed models.

Secondary outcomes including patient satisfaction, injection site reaction and engagement in treatment at follow-up will also be summarized.

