##### **3.1.1.4 Safety Population**

The safety population includes all participants who completed informed consent for the Ancillary component during the screening visit and received the XR-BUP injection. Pre-study participants are not included.

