## **3. Participant experienced a precipitated withdrawal within 1 hour of XR-BUP injection**

- Potential precipitated withdrawal events are adjudicated by study consultants and captured on the PWD eCRF as 'Yes' or 'No' at 240 minutes after the XR-BUP injection. If the time listed for this precipitated withdrawal is within 1 hour of the time of XR-BUP injection (including exactly 1 hour), the participant is considered to have experienced this outcome.
- In order for this outcome to be evaluable (i.e., non-missing), the PWD eCRF must be completed with a time of precipitated withdrawal provided one occurred.

For all three outcome measures, if the outcome measure is not evaluable (i.e., missing), the worst-case scenario will be imputed for that outcome measure where the participant is assumed to have experienced the outcome measure.

The *a priori* conditions on these outcomes in the Primary Ancillary Analysis population to inform expanding enrollment in the RCT component are:

- <20% of participants will experience a 5 or greater increase in COWS score within 4 hours of injection
- <10% of participants will transition to moderate withdrawal (COWS score 13 to 24, inclusive) within 4 hours of injection
- <10% of participants will experience precipitated withdrawal within 1 hour of injection

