Figure 3: Expected versus Actual Enrollments Overall (Full Ancillary Analysis Population)

[figure not shown]

| Table 3: Summary of Disposition (Full Ancillary Analysis Population)                 |                            |                      |                                     |                          |           |
|--------------------------------------------------------------------------------------|----------------------------|----------------------|-------------------------------------|--------------------------|-----------|
|                                                                                      | Yale-New Haven Hospital ED | Highland Hospital ED | Penn Presbyterian Medical Center ED | Rhode Island Hospital ED | Total     |
| Number of participants enrolled                                                      | N                          | N                    | N                                   | N                        | N         |
| Number of study completers                                               | N (xx.x%)                  | N (xx.x%)            | N (xx.x%)                           | N (xx.x%)                | N (xx.x%) |
| Number of active participants                                            | N (xx.x%)                  | N (xx.x%)            | N (xx.x%)                           | N (xx.x%)                | N (xx.x%) |
| Number of early study terminations                                       | N (xx.x%)                  | N (xx.x%)            | N (xx.x%)                           | N (xx.x%)                | N (xx.x%) |
| Number of early study termination participants receiving study drug      | N (xx.x%)                  | N (xx.x%)            | N (xx.x%)                           | N (xx.x%)                | N (xx.x%) |
| Number of early study termination participants not receiving study drug  |                            |                      |                                     |                          |           |
| Reason for early study termination                                       |                            |                      |                                     |                          |           |

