| Total                                                                                  |                 |                            |                                      |                      |                                                 |                      |

 Three COWS assessments are required: pre-injection COWS, and two post-injection COWS, one of which is within the last hour.

 The denominator is the number of participants enrolled.

| Table 13: Summary of Primary Outcome Analysis (Primary Ancillary Analysis Population) |                                                                                                      |           |                                      |
|---------------------------------------------------------------------------------------|------------------------------------------------------------------------------------------------------|-----------|--------------------------------------|
| Number Enrolled                                                                       | Primary Outcome Measure                                                                              | N (%)     | 95% Confidence Interval  |
| N                                                                                     | Participant experienced a 5 or greater increase in COWS score within 4 hours of the XR-BUP injection | N (xx.x%) | xx.xx% - xx.xx%                      |
|                                                                                       | Participant transitioned to moderate withdrawal within 4 hours of the XR-BUP injection               | N (xx.x%) | xx.xx% - xx.xx%                      |
|                                                                                       | Participant experienced a precipitated withdrawal within 1 hour of the XR-BUP injection              | N (xx.x%) | xx.xx% - xx.xx%                      |

Missing COWS scores or precipitated withdrawals are imputed as having experienced the event.

 Calculated using the Exact Clopper-Pearson method.

Table 14: Summary of Primary Outcome Analysis (Full Ancillary Analysis Population)

- repeat Table 13 for Full Ancillary Analysis population

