| Number of TEAEs                                                                               | N                               | N                         | N                                        | N                             | N          |
| Severity of TEAEs                                                                 |                                 |                           |                                          |                               |            |
| Grade 1 - Mild                                                                                | N (x.x%)                        | N (x.x%)                  | N (x.x%)                                 | N (x.x%)                      | N (x.x%)   |
| Grade 2 - Moderate                                                                            |                                 |                           |                                          |                               |            |
| Grade 3 - Severe                                                                              |                                 |                           |                                          |                               |            |
| Relationship of TEAE to study medication                                          |                                 |                           |                                          |                               |            |
| No                                                                                            | N (x.x%)                        | N (x.x%)                  | N (x.x%)                                 | N (x.x%)                      | N (x.x%)   |
| Yes                                                                                           |                                 |                           |                                          |                               |            |

 The percentage is calculated with the denominator as the number of participants enrolled.

 The percentage is calculated with the denominator as the number of participants with TEAEs.

 The percentage is calculated with the denominator as the number of TEAEs.

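### Ancillary participants who consent but are never injected stay in the primary denominator and are counted as events on both COWS outcomes (and on precipitated withdrawal if no form is completed)

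*Combined protocol and SAP*

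**What the plan says.** Four parts of the plan combine.

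- **Analysis set (SAP 3.1.1.2).** "The primary ancillary analysis population includes the first 75 planned participants who completed informed consent for the Ancillary component during screening". Injection is not required. The ancillary Safety Population (SAP 3.1.1.4) does require it: those who "completed informed consent for the Ancillary component during the screening visit and received the XR-BUP injection".
- **Outcomes (SAP 7.1.1).** The COWS rise of 5 or more and the transition to moderate withdrawal are measured over the 4 hours after injection. To be evaluable they need post-injection COWS scores, normally two, one of them in the last hour. Precipitated withdrawal is counted within 1 hour of injection and needs a completed precipitated withdrawal (PWD) form, which is tied to the 240-minute post-injection time point.
- **Missing outcomes (SAP 7.1.1).** If an outcome is not evaluable, "the worst-case scenario will be imputed for that outcome measure where the participant is assumed to have experienced the outcome measure". The footnote of the Table 13 shell repeats this. No exception is made for people who were not injected.
- **Criterion (SAP 7.1.2; protocol 12.6.6).** A condition is achieved only if the exact 95% upper limit is below it: 20% for the COWS rise and 10% for each of the other two. Protocol 12.6.6 writes the latter as "95% upper confidence limit < 10"%.

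The SAP allows for people who are not dosed. The disposition shell (Table 3) has a row headed "Number of early study termination participants not receiving study drug", the Table 12 shell separates enrolled from injected, and Listing 1 has a column for whether the injection was received.

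**The concern.** An un-injected participant cannot have a post-injection COWS score. Both COWS outcomes are then non-evaluable, and the rule turns them into events. Worst-case imputation is a reasonable, conservative choice for an injected person whose assessments were lost, because the outcome exists and was not seen. For a person who never received XR-BUP the outcome does not exist, and recording withdrawal after an injection that was not given is a miscoding rather than a missing-data assumption.

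The component asks how often XR-BUP given at a low COWS score is followed by withdrawal. As written, the headline rates, their intervals and the formal criteria mix that frequency with the frequency of leaving or declining before dosing.

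Some Safety Population shells err in the other direction. Table 22, footnote 1, states: "The percentage is calculated with the denominator as the number of participants enrolled". Table 26 (footnote 2) and Table 30 (footnote 4) also divide by participants enrolled. Read literally, these dilute rates in a population meant to contain only injected people.

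**Working it through.** **Inputs.** n = 75 (SAP 3.1.1.2); two-sided exact Clopper-Pearson limits at alpha = 0.05 (SAP 7.1.2); limits of 10%, 10% and 20% (SAP 7.1.1). The number un-injected, u, is not given; I assume a range of 0 to 5.

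**Formula.** For x events in n, the lower limit is the 0.025 quantile of Beta(x, n−x+1) and the upper limit is the 0.975 quantile of Beta(x+1, n−x). For x = 0 the upper limit is 1 − 0.025^(1/n).

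**Reproducing the plan's figure.** Taking x = 75p for the proportions in protocol Table 5 (repeated in SAP 10.1), the widths are 0.0664, 0.1134, 0.1485, 0.1732, 0.1918, 0.2062 and 0.2173. The plan states 0.066, 0.113, 0.148, 0.173, 0.192, 0.206 and 0.217. They agree within 0.0005.

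**Events each criterion allows at n = 75.**

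- 10% limit: 2 events give 9.30% (met); 3 give 11.25% (not met). At most 2.
- 20% limit: 8 events give 19.94% (met); 9 give 21.56% (not met). At most 8.
- A one-sided 95% limit leads to the same counts (3 events 10.01%, 9 events 20.01%).

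**Effect of u un-injected participants.** Each adds 1/75 = 1.33 percentage points to every outcome on which it is imputed. With no true event at all:

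| u | SAP rate, u/75 | SAP upper limit | Injected only, 0/(75−u), upper limit |
|---|---|---|---|
| 0 | 0% | 4.80% | 4.80% |
| 1 | 1.33% | 7.21% | 4.86% |
| 2 | 2.67% | 9.30% | 4.93% |
| 3 | 4.00% | 11.25% | 4.99% |
| 4 | 5.33% | 13.10% | 5.06% |
| 5 | 6.67% | 14.88% | 5.13% |

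From u = 3 a 10% criterion fails with no withdrawal observed. With 1 true event and u = 2, the SAP gives 3/75 (11.25%, fails) where the dosed give 1/73 (7.40%, passes).

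**Chance of meeting a 10% criterion if the true rate is 2% (an assumed value).** Under the SAP rule it is 56.3%, 22.9% and 0% for u = 1, 2 and 3. In injected participants it is 81.5%, 82.0% and 82.5%.

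**The 20% criterion.** The allowance is larger, so the effect is smaller. At an assumed true rate of 5% and u = 3, the chance of meeting it is 84.9% under the SAP rule and 97.3% in injected participants.

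**Does the plan's safeguard catch this?** SAP 7.1.4 makes complete-case and best-case analyses mandatory only when more than 5% of primary outcomes are missing in the Full Ancillary set (about 100). Three missing is 3% of about 100 (4% of 75), and five is 5%. None of these exceeds the trigger.

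**Full set.** At about 100, each un-injected participant adds about 1 point per outcome imputed.

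**The case against.** The strongest reply has four parts.

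- **The decision is past.** The conditions served one purpose: whether to open the RCT to lower COWS scores. Missing a condition led to DSMB review rather than refusal (SAP 11.2), and the protocol 8.10 addendum records DSMB concurrence in May 2021 with COWS 4-7. A reader might infer that the rule could still block the expansion, or that the expansion rests on a faulty test. The documents support neither. The reported rates, intervals and criteria are still affected.
- **Cleaner results are already planned.** SAP 8.1.1 (Table 20 shell) tabulates these events in the injected Safety Population, SAP 7.1.4 permits complete-case analysis, and Listing 1 identifies the un-injected. This helps in part. Table 20 has no confidence intervals, its precipitated-withdrawal column covers the 4-hour capture and not the 1-hour outcome, and the complete-case analysis is optional up to 5% missing.
- **The count may be zero.** A row in a blank shell shows that the table allows for undosed people, not that there were any. The Table 16 footnote mentions one participant with a missing baseline COWS score but does not say whether that person was injected. This objection stands: no actual inflation can be claimed.
- **The rule is open and errs against the drug.** True, but the stated aim is to estimate proportions, and SAP 9.1 says no hypothesis is tested. Conservatism does not justify assigning an outcome to someone who was not exposed.

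Three further inferences go too far. Un-injected participants are not necessarily counted as precipitated withdrawals, because a PWD form completed as No would be evaluable as a non-event. The two-event allowance does not apply to all three outcomes, since the COWS rise allows 8. The shells are not wrong throughout either: Table 12 reports data availability, so its footnote "The denominator is the number of participants enrolled" is reasonable. Many other denominators are correctly events or assessments, and the Table 22 wording may simply be loose.

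**Conclusion.** The point holds in this form. As written, SAP 3.1.1.2 with 7.1.1 scores consented but un-injected participants as events on the two COWS outcomes, and on precipitated withdrawal when no PWD form is completed. The cost is 1.33 percentage points per person per outcome imputed at n = 75. Three such people and no true event would fail a 10% criterion (11.25% against 4.99% in the 72 dosed) without requiring a sensitivity analysis.

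This rests on two assumptions. First, at least one of the first 75 was not injected; otherwise nothing changes. Second, the criteria are read on the upper confidence limit, as protocol 12.6.6 and SAP 7.1.2 state. Protocol 8.10 and 9.13 give plain percentages. On that reading 7 of 75 (9.3%) would still be below 10%, and three un-injected participants (4.0%) would not cause a failure, although the rates would still be wrong.

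**What to change.** 1. Estimate the three primary outcomes, with exact intervals, in participants among the first 75 who received the injection. Do the same in all injected participants for the full set.
2. Keep worst-case imputation only for injected participants with missing assessments. State this against protocol 12.6.1, which says that primary and secondary analyses will not impute.
3. Show the current consented-set result alongside as a labelled sensitivity analysis. Results for the first 75 went to the DSMB in April 2021, so a change that favours the drug should be visible.
4. Report the un-injected count in disposition.
5. Change only the participants-enrolled denominators to number injected in Table 22 (footnote 1), Table 26 (footnote 2) and Table 30 (footnote 4). Leave the event- and assessment-based denominators and Table 12 as they are.

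**Cost.** SAP wording, three footnotes and one extra display. The denominator falls slightly below 75. At n = 70 to 74 the 10% criteria still allow 2 events (upper limits 9.94% to 9.42%), now all observed. The 20% criterion allows 7 instead of 8 (8/74 gives 20.2%). That is no loss in practice: with u of 1 or more, the current rule leaves room for only 8 − u true events, which is 7 or fewer.

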##### **3.1.1.3 Full Ancillary Analysis Population**

The full ancillary analysis population includes all participants who completed informed consent for the Ancillary component during screening. Pre-study participants are not included.

##### **3.1.1.4 Safety Population**

The safety population includes all participants who completed informed consent for the Ancillary component during the screening visit and received the XR-BUP injection. Pre-study participants are not included.

##### **3.1.1.5 General Definitions**

##### **3.1.1.6 Index ED Visit**

The Index ED Visit is the first visit for participants and involves both screening and enrollment.

##### **3.1.1.7 Study Day**

Study Day (or Day) is defined as the number of days post-index ED Visit with Study Day 0 defined as the date of enrollment.

##### **3.1.1.8 7-day Follow-Up Visit**

The 7-day follow-up visit date is defined as the seventh study day. The actual visit can occur later, but information is only collected about events that occurred within 7 days of the index visit.

##### **3.1.1.9 Safety Window**

The safety window for all participants enrolled in the Ancillary component will begin on date of the study injection and end up to 7 days afterwards.

##### **3.1.1.10 Baseline COWS Score**

The baseline COWS score is defined as the COWS score entered on the COW eCRF at the baseline/pre-injection visit after enrollment (visit B000). If this is not available because less than 30 minutes elapsed from the baseline/pre-injection visit and the COWS score completed to determine eligibility (as indicated by the CONOBLCW variable on the COW eCRF), then the COWS score entered on the COW eCRF at the screening visit (visit A1) is the baseline COWS score. Otherwise, the baseline COWS score is missing.

## **3.2 RCT Component**

### **3.2.1 Analysis Populations**

If a participant is mistakenly randomized twice, only the first randomization will be included in the study populations and associated analyses.

#### **3.2.1.1 Intent-to-Treat (ITT) Population**

The ITT population consists of all ED participants who provided informed consent and were randomized into the study. ITT analyses will be performed according to the participant's randomized treatment arm.

#### **3.2.1.2 Per Protocol (PP) Population**

The Per Protocol (PP) population will be a subset of the ITT population and exclude participants who did not receive study treatment as randomized such as refusing the injection, leaving the ED before medication could be administered, or opting for home induction in participants with COWS  $\geq 8$ . The PP population will also exclude participants who were enrolled and later found to be ineligible based on the inclusion and exclusion criteria. PP analyses will be performed according to the participant's actual treatment arm.

